##### Homework Completion

Effects of the app on homework completion will be analyzed separately for homework quantity and quality. Psychometric properties of the measures will be examined and correlations will be computed to examine congruence between adolescent and therapist sources of information. If warranted, aggregate scores will be computed; otherwise, separate analyses will be done using different measures. To test the hypothesis that the quantity and quality of homework will be greater in the app compared with the no-app group, we will test group differences in quantity and quality scores. We will also explore timing effects, given evidence suggesting that homework completion varies over time and may decrease over the course of treatment [36]. Scores for the first 4, middle 4, and final 3 weeks of homework will be averaged, creating 3 assessment points, and a mixed-model repeated measures multivariate analysis of the variance will be performed with the between factor of group (app vs no-app), the within factor of time (early, middle, late), and the 2-way interaction of group × time.

Exploratory analyses will also be performed. Subgroup analyses will explore differences in the app’s impact on homework completion as a function of test site and gender. Correlations will explore relations between cognitive profiles and homework completion. For the app group, psychiatric and cognitive assessment data will be aggregated and advanced analytics will be performed to examine predictive relations between patient attributes (anxiety, depression, cognitive profile) and the quantity and quality of homework completion. These analyses will include homework completion data logged by the app (proportion of the task completed, the time spent on the task, and the number of visits to the assignment page).

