#### Sample Size and Power

Given the low rates of homework completion in research to date, we expect that the app will have at least a moderate effect on homework completion compared with the no-app group [28,35,36]. A power calculation, based on a comparison between 2 groups (app vs no-app) across 4 occasions (pre, post, follow-up 1, follow-up 2) for a single measure, indicates that a sample size of 35 for each group would provide power of 0.84 to detect a moderate effect size for homework completion at α = .05. To allow for dropouts [98], we will recruit 100 youth between 12 and 18 years of age (10 per group at each site). As noted earlier, treatment dropout rates can be substantial and adherence to homework is often quite low. This has been taken into account in calculating the sample size. The expectation is that compliance will be greater for the app than the no-app group. Based on previous research with youth [98], we expect a 10% rate of attrition at each of the 2 follow-ups.

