#### Measures

At pretreatment, as in Phase 2, we will assess (1) demographic characteristics and comfort with technology to characterize the sample, and (2) cognitive skills to examine associations between cognitive profiles and homework completion as well as user experience.

During treatment, homework completion will be assessed weekly. The quantity (amount) as well as the quality (appropriateness) of homework will be assessed, based on evidence that they both relate to treatment outcome [99]. Multiple sources of homework information (adolescent, therapist, data logged by the app) will be obtained to address potential differences between sources [99,100]. Adolescents will assess the quantity and quality of their homework upon arriving at the session, by rating on a 5-point scale how much of it was completed and how well it was done, using 2 items from the Homework Rating Scale II [101], an internally consistent measure of homework quantity and quality developed for use with adults [102]. The 2 items have not previously been tested with adolescents and will be pilot-tested in this study. Two additional measures of homework quantity will be obtained by asking adolescents to estimate the number of days and the number of hours they spent doing homework [103]. Therapists will assess homework completion following the session. They will assess homework quantity by rating the proportion of assigned homework that was completed (from 0% to 100%), a method used in previous research [36,103]. They will rate the quality of the work on a 6-point scale [104], using criteria specified for each assignment; this measure has been found to predict treatment outcome [103]. A third source of information about homework quantity will be obtained in the app group from data logged by the app: the proportion of the task completed, the time spent on the task, and the number of visits to the assignment page.

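### The main homework hypothesis may be tested on two aggregates or up to six separate measures, with no pooling criterion, lead measure or success rule, although power was set for one measure

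*Protocol article*

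**What the plan says.** Greater homework adherence in the app group is the stated hypothesis of Phase 3, so this is the main test and not an exploratory one.

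The Measures section lists these homework measures for both groups:

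- **Quantity (4):** the adolescent's rating of how much was done, the adolescent's estimate of days, the adolescent's estimate of hours, and the therapist's percentage.
- **Quality (2):** the adolescent's rating of how well it was done, and the therapist's 6-point rating.

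Three further quantity measures logged by the app exist in the app group only and cannot be compared between groups. Of the two adolescent rating items the section says: "The 2 items have not previously been tested with adolescents and will be pilot-tested in this study". The therapist quantity measure is obtained by "rating the proportion of assigned homework that was completed (from 0% to 100%), a method used in previous research".

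The Homework Completion section analyses quantity and quality separately. It first examines psychometric properties and the agreement between adolescent and therapist, and then: "If warranted, aggregate scores will be computed; otherwise, separate analyses will be done using different measures".

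The Sample Size and Power section assumes a moderate effect and α = .05, and states that "a sample size of 35 for each group would provide power of 0.84". The calculation is made "for a single measure", which is not named.

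**The concern.** The sample size is justified for one test, while the analysis section commits to at least two and allows six. What decides between them is whether pooling is warranted, a word to which no threshold is attached. Nothing says which result carries the hypothesis if the measures disagree. Disagreement is foreseeable, because the protocol collects several sources precisely because they may differ.

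Two things are at stake. A claim that the app works could rest on whichever of several measures came out positive, at an error rate above the nominal one. And if adolescents and therapists gave conflicting results, there would be no agreed reading of the trial's main question.

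**Working it through.** **1. The stated power.** Inputs from Sample Size and Power: 35 per group, 4 occasions, α = .05, a moderate effect. No numeric effect size, within-person correlation or sidedness is given. I assume f = 0.25 (equivalently d = 0.5).

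- A plain two-sided two-sample t test with d = 0.5 and 35 per group has power 0.54.
- For the between-group test in a repeated-measures analysis, the noncentrality is λ = N f² m / (1 + (m − 1)ρ). With N = 70, m = 4 and ρ = 0.316, λ = 70 × 0.0625 × 4 / 1.948 = 17.5 / 1.948 = 8.98, and power is 0.84.

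So 0.84 is attainable at a correlation near 0.32, but it cannot be confirmed from the text. What matters here is that it belongs to one measure tested once at .05.

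**2. Number of tests.** Six measures in both groups (4 + 2) if kept separate; two if pooled within quantity and within quality. Six is a maximum.

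**3. Chance of at least one false positive.** Assumptions: no true difference, each test two-sided at 0.05, any one positive result counts. For independent tests this is 1 − 0.95^k:

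- k = 6: 1 − 0.95⁶ = 0.265
- k = 2: 1 − 0.95² = 0.0975

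For results favouring the app only, it is 1 − 0.975^k:

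- k = 6: 1 − 0.975⁶ = 0.141
- k = 2: 1 − 0.975² = 0.049

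For correlated tests I simulated equally correlated normal test statistics (1,000,000 draws):

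| Correlation | 6 tests, either direction | 6 tests, favouring app | 2 tests, either direction | 2 tests, favouring app |
|---|---|---|---|---|
| 0.3 | 0.241 | 0.122 | 0.095 | 0.048 |
| 0.5 | 0.207 | 0.104 | 0.090 | 0.045 |
| 0.7 | 0.165 | 0.083 | 0.083 | 0.042 |
| 0.8 | 0.138 | 0.069 | 0.078 | 0.039 |

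The benchmarks are 0.05 in either direction and 0.025 favouring the app.

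**4. The joint reading.** If quantity and quality aggregates must both be significant, the chance that both are falsely positive cannot exceed the chance for either alone. It is therefore at most 0.05, and there is no inflation.

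**5. What a late correction would cost.** I hold λ = 8.98 at 35 per group, scale it with sample size, and apply Bonferroni. Power per measure:

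| Evaluable per group | 1 test at 0.05 | 2 tests at 0.025 | 6 tests at 0.0083 |
|---|---|---|---|
| 35 | 0.84 | 0.76 | 0.61 |
| 40 | 0.89 | 0.82 | 0.69 |
| 50 | 0.94 | 0.90 | 0.81 |

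Keeping 0.84 takes about 43 per group for two tests and about 54 for six. The plan recruits 50 per group.

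**The case against.** **The percentages overstate the harm if read as false claims of benefit.** A reader might take 26% as the chance of wrongly concluding that the app helps. It is not: it includes false findings against the app. The figures in the app's favour are about half, and for two aggregates they are 4% to 5%. This objection stands. What remains is a rate of up to about twice the nominal 2.5% for two aggregates and several times that for six tests.

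**The choice is not made on group differences.** A reader might infer that the sponsor could look at the treatment effects and then choose. The inputs named are psychometric properties and correlations between sources. Checking them is sensible when two items are new to this age group, and it could be done blind to group. This also stands. The error rates above come from the number of tests, not from the pooling choice. The text does not say that the check is blind, however, and it sets no threshold.

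**Neither end of the range is likely.** Highly correlated sources would probably be pooled, and four of the six measures are one adolescent's reports on the same homework, so independence is implausible. This is fair, and the middle of the range is the better guide.

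**The hypothesis is worded jointly, for quantity and quality together.** Under that reading the two-aggregate route is not inflated. But the section never says that both must succeed, and it gives no rule for six separate measures.

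**The planned analysis is multivariate.** That analysis is introduced for timing effects (group, time and their interaction). It is not presented as a joint test controlling error across measures.

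**An unseen analysis plan may settle this.** It could supply a threshold and a multiplicity method. Silence on those details alone would not be a finding. But here the article itself fixes the main test as an open choice, beside a power calculation for one unnamed measure.

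**Conclusion.** The point holds in a limited form. The protocol article leaves the test of its main hypothesis open between two aggregates and up to six measures, with no criterion, lead measure or success rule, and the sample size rests on one measure.

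If any one positive result counts and each test is two-sided at 0.05, the either-direction error is 26% for six independent tests, about 21% at correlation 0.5, and 9% to 10% for two aggregates at correlations up to 0.5. In the app's favour it is about 14%, 10% and 4% to 5%, against 2.5%. These figures rest on assumptions the text does not state: the any-one-counts rule, two-sided testing at 0.05 for each measure, and equal correlations.

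The documents do not support saying that the measure will be picked on its treatment effect, that six tests will certainly be run, or that the stated power of 0.84 is wrong.

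**What to change.** Before any between-group data are seen:

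1. Name one primary homework measure available in both groups and test it once at two-sided 0.05. Two options are the therapist-rated percentage completed, averaged over the weekly assignments (4 + 4 + 3 = 11 weeks in the planned time blocks), or a quantity aggregate whose components are fixed in advance.
2. Test quality only if the primary result is significant, or state that quantity and quality must both be significant.
3. Report the remaining measures as supportive.
4. Make any pooling check on data pooled over groups, blind to assignment, with the threshold written down.

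This takes about a paragraph, with no extra participants or data. The single-test route keeps the stated 0.84. Requiring both lowers power: if each has 0.84 and they were independent, joint power is 0.84 × 0.84 = 0.71, rising towards 0.84 as they become more correlated.

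There are two real costs. The sponsor has fewer routes to a positive claim. And therapists know the group: the Feasibility and Requirements Analysis section describes a therapist portal giving access to homework results with the adolescent's consent, while the no-app group uses paper. The therapist percentage may therefore be ascertained differently in the two groups. If it is chosen, show the adolescent-rated results beside it as a sensitivity check, bearing in mind that adolescents also know their group.

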#### Study Design

We will conduct a multisite, randomized controlled pragmatic clinical trial in routine clinical settings to test the app’s effectiveness under real-world conditions in order to enhance external validity and ensure successful implementation without sacrificing scientific rigor. A pragmatic clinical trial also suits the nature of mHealth technologies, which require ongoing improvement and are subject to rapid technological change [95-97]. After pretreatment assessment, participants will be randomly assigned to receive a manualized CBT treatment either with app support (app group) or without it (no-app group). Youth assigned to CBT with the app will receive CBT treatment for 12 weeks with the app included (app group). They and their therapists will be shown how to use the app. Youth assigned to receive CBT treatment for 12 weeks with paper-based homework will be in an active control condition (no-app group). Both groups will be in treatment for 12 weeks, the typical duration of CBT. However, therapists in both the app and no-app groups will be able to provide additional sessions should they deem it clinically relevant. Duration of CBT will be recorded and group differences will be analyzed. Following the pretreatment assessment and exclusions, participants providing informed consent will be randomly assigned to treatment group. Random assignment will be done at each test site separately by the site coordinator. At each site, half the participants will be assigned to each group in order to control for site-specific variables (eg, type of CBT delivered, professional background of therapist). To assess the app’s effectiveness both immediately and over time, assessments will be done at the end of the 12-week treatment (posttreatment) and again after 6 months (follow-up 1) and 12 months (follow-up 2). At each time-point, participants will receive a CAD$30 gift card as an honorarium.

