#### Data Analysis

To assess the app’s effectiveness, differences between the app and no-app groups will be examined with respect to homework completion. We will also explore group differences in treatment outcomes. Although randomization will be used to mitigate group differences, potential differences between groups will be examined. If differences are found on variables that may be related to homework completion or treatment outcome (symptom severity/diagnosis, age, sex distribution, history of psychotherapy and pharmacological interventions, comorbid mental health problems, therapist), these variables will be included as covariates in the analyses. Descriptive analyses will be performed on demographic characteristics, comfort with computers, and retention rates (participants assessed at posttreatment and follow-ups). To avoid bias in parameter estimates, missing data will be handled by performing intent-to-treat analyses, in which missing values are replaced using the last observation carried forward, a method appropriate for randomized designs [114].

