##### Client Satisfaction With Service

To examine differences between the app versus no-app groups in client satisfaction, a *t*-test will be performed on total CSQ scores. Levels of satisfaction will be compared with norms established in other studies of youth in CBT treatment [111,121].

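### Therapist enters the homework analysis only if the arms differ on it, which is the wrong rule for a clustering factor; how much this matters depends on a therapist-by-arm arrangement the protocol does not state

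*Protocol article*

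**What the plan says.** All references are to Phase 3 of the protocol article.

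- **Study Design.** Individual youths are randomised within site: "Random assignment will be done at each test site separately by the site coordinator". Half of each site goes to each arm, and therapists' professional background is given as one of the site features this is meant to control. Allocation is not within therapist.
- **Measures.** Therapists rate homework after each session. "They will assess homework quantity by rating the proportion of assigned homework that was completed (from 0% to 100"%), and they rate quality on a 6-point scale. Adolescents give their own ratings of quantity and quality and estimate days and hours spent.
- **Data Analysis.** Therapist closes a list of variables that may relate to homework completion or treatment outcome. They are used only if the arms are found to differ on them: "comorbid mental health problems, therapist), these variables will be included as covariates in the analyses".
- **Homework Completion.** The only model named is "a mixed-model repeated measures multivariate analysis of the variance will be performed with the between factor of group (app vs no-app"), time (early, middle, late) and their interaction.
- **Client Satisfaction With Service.** "a *t*-test will be performed on total CSQ scores".
- **Sample Size and Power.** "a sample size of 35 for each group would provide power of 0.84", with no ICC or design effect.

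**The concern.** The named model allows for repeated scores within a youth but otherwise treats youths as independent. Youths with the same therapist share that therapist's way of setting and reviewing homework and, for the therapist-rated measures, the same rater's leniency. The protocol itself accepts that therapist may be related to homework completion, so a non-zero therapist ICC is plausible on its own terms.

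The article does not leave therapist open; it fixes a rule, and the rule answers a different question. Checking whether the arms differ on therapist addresses chance confounding. It says nothing about correlation between youths of the same therapist:

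- If therapists are balanced over the arms, the trigger does not fire and the therapist variance stays in the error term.
- If therapists are partly unbalanced and therapist enters as a fixed factor, it is partly collinear with group and costs precision.
- If each therapist works in one arm, the trigger is bound to fire. The group indicator is then the sum of that arm's therapist indicators, so a fixed therapist factor leaves no estimable app effect.

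At stake is the standard error of the app versus no-app comparison, and in the last case whether it can be estimated at all.

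**Working it through.** **Inputs from the protocol (Study Design; Sample Size and Power).** 100 youths, 50 per arm, 10 per arm at each of 5 sites; 35 per arm for power 0.84; alpha 0.05, taken as two-sided.

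**Assumptions, because the protocol gives none of these.** Therapist ICC 0.05, 0.10 and 0.20; m youths per therapist; therapists shared between arms or confined to one arm.

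**The plan's own figure.** The effect is called moderate, without a number. With f = 0.25, N = 70, 4 occasions and within-person correlation ρ, the between-group F test has noncentrality λ = f²·N·4 / (1 + 3ρ) = 17.5 / (1 + 3ρ) on 1 and 68 df.

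- ρ = 0.30: λ = 17.5 / 1.90 = 9.21, power 0.849
- ρ = 0.32: λ = 17.5 / 1.96 = 8.93, power 0.838
- ρ = 0.50: λ = 17.5 / 2.50 = 7.00, power 0.742

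The stated 0.84 is therefore reached at ρ of about 0.3, a value not given, and with independent youths.

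**Case 1: therapists treat both arms in balance, term omitted.** The contrast has variance proportional to 1 − ICC, while the test uses roughly the total variance. Type I error ≈ 2[1 − Φ(1.96/√(1 − ICC))]. Power is at 35 per arm, for the effect giving 0.84 with independent youths.

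| ICC | Type I error | Power, term omitted | Power, term included |
|---|---|---|---|
| 0.05 | 0.044 | 0.846 | 0.858 |
| 0.10 | 0.039 | 0.853 | 0.876 |
| 0.20 | 0.028 | 0.867 | 0.910 |

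The loss is 1.2, 2.3 and 4.3 points.

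**Case 2: therapists shared, allocation ignores therapist.** Simulation of the unadjusted test on youth means (20,000 runs per setting, 2 or 4 therapists per site, 35 or 50 per arm) gives type I error of 0.039 to 0.050 over the same ICC range.

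**Case 3: each therapist in one arm, term omitted.** Design effect D = 1 + (m − 1)·ICC; type I error ≈ 2[1 − Φ(1.96/√D)].

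| m | ICC | D | Type I error | Simulated, 50 per arm |
|---|---|---|---|---|
| 2 | 0.05 | 1.05 | 0.056 | – |
| 3 | 0.05 | 1.10 | 0.062 | – |
| 5 | 0.05 | 1.20 | 0.074 | 0.073 |
| 5 | 0.10 | 1.40 | 0.098 | 0.098 |
| 5 | 0.20 | 1.80 | 0.144 | 0.149 |
| 10 | 0.05 | 1.45 | 0.104 | 0.108 |
| 10 | 0.10 | 1.90 | 0.155 | 0.159 |
| 10 | 0.20 | 2.80 | 0.241 | 0.249 |

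**Power of a test that allows for clustering in Case 3.** Take the effect that gives 0.84 with 35 independent youths per arm, and 50/D effective youths per arm. Power at ICC 0.05 / 0.10 / 0.20 is 0.90 / 0.85 / 0.75 for m = 5 and 0.84 / 0.73 / 0.56 for m = 10. Recruiting 50 rather than 35 absorbs a design effect of up to 50/35 = 1.43 if homework data are nearly complete. These are normal approximations. At m = 10 there are only 10 therapists and 8 df, so true power is lower: at d = 0.5 and ICC 0.05, about 45% rather than 55%.

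**The case against.** The strongest reply is that the protocol does not establish any error in the main test. A reader might infer that the false-positive rate is inflated, or that lenient raters will look like an app effect. That needs therapists confined to one arm, which the protocol never states. Youths are randomised individually within site. The references to therapists in both groups, and to the app group's youth and therapists, are compatible with separate therapists per arm but do not show it. If therapists are shared, the error rate is at or below nominal. Even with separate therapists, 2 or 3 youths each at ICC 0.05 gives only about 6%, and the interprofessional staffing described under Implementation Plan makes more than one therapist per arm and site quite possible. All of this stands.

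Two further points stand in part. The named model follows the sentence on timing effects, and the hypothesis sentence before it names no method; still, it is the only homework model given, and the covariate rule covers the analyses generally. Rater leniency affects only the therapist ratings, not the adolescents' self-reports; the shared influence of the therapist's delivery could affect both.

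It could also be said that random effects and degrees of freedom belong in the full protocol or SAP. That would excuse silence. It does not excuse a stated rule that makes therapist adjustment depend on observed imbalance.

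**Conclusion.** The imbalance-triggered covariate rule for therapist is unsuitable under every arrangement the protocol leaves open, and the named homework model and the satisfaction t-test make no other allowance for clustering. The consequence is conditional. With shared therapists it is small: an error rate of about 3 to 5% and, when the split is balanced, 1 to 4 points of power lost at 35 per arm. With therapists confined to one arm and ICC 0.05 to 0.20, type I error is about 7 to 15% at 5 youths per therapist and 10 to 25% at 10. Applying the rule with a fixed therapist factor would then leave the app effect inestimable. ICC, caseload and arrangement are all assumptions here. The point is worth acting on because the correction is cheap and works in each case, not because inflation has been shown.

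**What to change.** In Data Analysis and Homework Completion:

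1. State whether each therapist treats both arms, and roughly how many youths each will treat.
2. Remove therapist from the list of covariates added only when the arms differ.
3. Analyse homework quantity and quality in a linear mixed model with group, time, group by time and site, and random intercepts for youth and therapist, included whatever the observed balance, with Kenward-Roger or Satterthwaite degrees of freedom.
4. In Client Satisfaction With Service, replace the plain t-test with a comparison that includes the same therapist random intercept.
5. Record the treating therapist's code with each rating.
6. Restate power over an assumed ICC range.

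The cost is wording and one recorded field, with no extra participants or visits. With few therapists the therapist variance will be imprecisely estimated. If therapists work in one arm only, intervals will be materially wider: at 10 youths per therapist the standard error grows by √1.45 = 1.20 (20%) at ICC 0.05 and √2.80 = 1.67 (67%) at ICC 0.20. That width reflects the information the design would actually hold.
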